### Sample size calculation and statistical analysis

The ENABLE-Hip trial has been designed as a two-arm non-inferiority trial for a binary study endpoint with a single interim analysis. The required total sample size needed to ensure a global one-sided significance level of 5% and a global power of 80% was computed using a normal approximation. The adaption strategy is based on a group sequential design with an interim analysis when 60% of the initially planned patients have completed the 3-month follow-up. Sample size recalculation using the conditional error function approach is planned at the interim analysis, and stop for futility is possible. No early stop for efficacy is planned.

A sample size of 2,786 evaluable patients has been calculated. Taking into account a possible censoring (i.e., dropout) rate of 5%, 2,932 patients need to be included in the trial. The assumptions for calculating the sample size were based on largely consistent existing data. More specifically, a pooled analysis[31] of 14 randomized controlled trials cited by the American College of Clinical Pharmacy (ACCP) guidelines on VTE prophylaxis after orthopedic surgery [5], yielded a symptomatic DVT rate of 1.27% after prophylactic LMWH use. Data from a prospective database of hospital-acquired VTE after THA or TKA in the United Kingdom revealed a similar VTE (DVT or PE) rate of 1.11% [32]. Based on these data and on Canadian experience, a large randomized controlled trial on brief (5-day) postoperative anticoagulation followed by ASA versus standard-duration anticoagulation assumed a 3-month VTE probability of 1.0% in the standard-of-care arm [13]. Although that trial eventually found VTE in only 0.64–0.70% of the patients in either arm [13], a 1.0% probability in the control arm remains an appropriate estimate as the results of the other studies mentioned above appear to be supported by a registry on total joint arthroplasty in the United States [33]. For the experimental arm, the estimated rate of ≥ 2% as per **H**_**0**_ corresponds to a ‘minimal clinically significant difference’ of 1.0% compared to the standard of care. This margin is medically sensible, considering that approximately 1 out of 25 (post-THA) VTE events that *might* occur due to a shorter anticoagulation period may be life-threatening, which has to be viewed against an up to 10% expected case-fatality rate of major hemorrhage associated with (longer) anticoagulation (reviewed in [13]). Finally, the assumption of a low frequency (1.0% or even less) of VTE events as per H_1_ is justified by the results of a nationwide prospective Danish cohort study, in which anticoagulation treatment (not followed by ASA) was given for the duration of hospitalization if it was less than 5 days [15].

The primary efficacy endpoint will be analyzed in the per-protocol (PP) population and in the modified intention-to-treat population (mITT). The PP population consists of all patients who have (i) signed the informed consent; (ii) undergone randomization and the planned surgical procedure (THA); and (iii) completed the study without major protocol deviations. The mITT population includes all randomized patients who underwent THA and received at least one dose of the study medication.

In case of poor protocol adherence, the duration of study treatment would be shortened similarly in both treatment arms (since this is a double-blind trial), and this would affect efficacy particularly in the control intervention arm in which active treatment duration is longer. On the other hand, if there were protocol violations leading to arbitrary discontinuation of study treatment and prescription of open-label rivaroxaban after day 10, these would happen with equal frequency in both groups, again given the double-blind design. Either scenario would result in attenuation or elimination of the differences in the ITT population, favoring demonstration of ‘non-inferiority’. For these reasons, testing for non-inferiority in the PP population is considered the most rigorous approach in such a setting [34, 35]. Nonetheless, as a European Medicines Agency (EMA) Reflection Paper suggests that the full analysis set (ITT) and the PP analysis set both have equal importance [36], the primary endpoint will be analyzed in both populations and non-inferiority will be declared if it can be established in both.

H_0_: p_E_–p_C_ ≥ δ, with δ = 0.01, where p_E_ and p_C_ are symptomatic VTE probability within 3 months in the experimental (p_E_) and control group (p_C_) respectively, will be tested against H_1_, p_E_–p_C_ < δ, with δ = 0.01. The test will be implemented by comparing the cumulative incidence of VTE at 3 months using the complementary log–log transformation [37]. Comparisons will be adjusted for stratum. Point estimates of the cumulative incidence will be obtained using the Kaplan–Meier method. To account for patients completing only part of the follow-up, tests based on the cumulative incidence will be used.

Categorical outcomes will be described by absolute and relative frequencies in each treatment group with the corresponding 95% confidence interval (CI). Comparisons will be made using logistic regression with treatment as explanatory variable and adjusting for stratum. Quantitative outcomes will be summarized by treatment group as means with standard deviation, and/or as medians with minimum, maximum values and interquartile range, as appropriate. Comparisons will be based on linear regression models with treatment as explanatory variable and adjusting for stratum, or on stratified Wilcoxon-Mann–Whitney tests. Time-to-event outcomes will be described by Kaplan–Meier estimates in each treatment group and compared using stratified log-rank tests. Exploratory tests will be two-sided at the 5% significance level and the CI will be two-sided 95% CI unless stated otherwise.

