1) Written informed consent 2) Age between 18 and 85 years 3) Scheduled to undergo elective unilateral primary THA and eligible for perioperative management based on the ERAS protocol 4) Baseline TUG test scoring < 20 s, corresponding to a good mobility status before surgery 5) Capability to understand and comply with the protocol requirements (e.g., to answer the questionnaires) 6) Negative serum pregnancy test and and highly effective method of contraception for the duration of study treatment	1) Previous DVT or PE 2) Hip or lower limb fracture in the previous three months 3) Major surgical procedure within the previous three months 4) Active cancer (metastatic or requiring chemotherapy or radiation therapy) 5) Active peptic ulcer disease, gastritis, or prior gastrointestinal bleeding 6) Obesity with body mass index (BMI) > 40 kg/m^2^ body surface area 7) Severe renal impairment defined as estimated glomerular filtration rate < 30 ml/min 8) Severe hepatic impairment defined as Child Pugh Class B or C 9) Uncontrolled intercurrent illness (i.e., active infection, symptomatic congestive heart failure, uncontrolled hypertension, unstable angina pectoris, interstitial lung disease, serious gastrointestinal conditions, psychiatric illness) 10) Active or recent major bleeding at any site, or any disease or condition which, in the investigator’s jedgement, may significantly increase the bleeding risk during postoperative anticoagulation 11) Contraindication to discharge within 6 days after surgery 12) Expected requirement for major surgery within a 90-day period post THA 13) Need for long-term anticoagulation (e.g., atrial fibrillation, previous VTE) 14) Need for chronic antiplatelet therapy except for acetyl salicylic acid at a dose ≤ 100 mg daily or clopidogrel 75 mg daily 15) Previous participation in this trial 16) Life expectancy < 6 months 17) Participation in another interventional clinical trial at inclusion or within the last 30 days prior to inclusion, except during the observational follow-up period of that rial 18) History of hypersensitivity to the investigational medicinal product or to any drug with similar chemical structure or to any excipient in its pharmaceutical form

DVT: deep vein thrombosis; ERAS: enhanced recovery after surgery; PE: pulmonary embolism; THA: total hip arthroplasty; TUG: Timed Up and Go; VTE: venous thromboembolism

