The trial flow diagram is shown in Graphical Abstract. After confirmation of eligibility criteria (Table 1) and obtaining written informed consent, subjects will be randomly assigned to one of the above treatment groups. Treatment assignment will be performed via the electronic case report form (eCRF) on Visit 1 (day -10 to day -1 before surgery). A randomization/treatment assignment list will be generated by the Institute of Medical Biostatistics, Epidemiology and Informatics (IMBEI) at the University Medical Center Mainz. The randomization ratio of the experimental treatment group and the control treatment group will be 1:1. In order to account for possible differences in the initial open-label period of prophylactic anticoagulation as per local standard, randomization will be performed per site. Additionally, randomization will be stratified by concomitant single chronic antiplatelet medication (ASA or clopidogrel). Block randomization with varying block length will be applied. Considering that 10–15 centers are expected to recruit a total of 2,932 patients into the trial (see below), we anticipate 20 strata with sizes between 100 and 150.

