^b^Blood pressure, pulse rate, respiratory rate, arterial or capillary blood oxygen saturation, body temperature

^c^Sodium, potassium, calcium, magnesium, chloride, glucose, creatinine, estimated glomerular filtration rate (eGFR), alanine aminotransferase (ALT), γ-glutamyltransferase (γ-GT), international normalized ratio (INR), activated partial thromboplastin time (aPTT)

^d^Leukocyte (total white blood cell count, basophils, eosinophils, neutrophils, monocytes, lymphocytes), erythrocyte and platelet count, hemoglobin, hematocrit

^e^Required for women of childbearing potential (i.e., all women until 2 years post-menopausal)

^f^The study medication kit will be dispensed once, either at Visit 2 or Visit 3, but in any case, before or on day 3 after surgery

^g^Diagnostic work-up of clinically suspected deep vein thrombosis or pulmonary embolism as per current guideline recommendations (no screening in asymptomatic patients)

**Table 3 Tab3:** Primary and secondary endpoints

Primary endpoint	Secondary endpoints
Acute symptomatic or fatal VTE, defined as (i) symptomatic DVT of the popliteal or more proximal leg veins (femoral or iliac veins) or inferior vena cava; or (ii) symptomatic (segmental or more proximal) or fatal PE, occurring in the first 90 days after surgery and confirmed by objective testing Safety endpoint: Overt major or clinically relevant non-major bleeding	(1) Death from any cause (2) Isolated symptomatic distal DVT (3) Myocardial infarction or stroke (4) Need for readmission to the hospital (5) Length of hospital stay (6) Serious adverse events (SAEs) (7) Patient mobility (8) Changes in patient-reported hip joint-specific disability measured by the HOOS-12 score following surgery (9) Generic quality of life measured by EQ-5D-5L All within 3 months of the surgical intervention and using standardized scores and questionnaires Postoperative healthcare resource utilization will be assessed at 35 days after surgery

DVT: deep vein thrombosis; ERAS: Enhanced Recovery After Surgery (protocol); HOOS: Hip disability and Osteoarthritis Outcome; PE: pulmonary embolism

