The safety endpoint is overt major or clinically relevant non-major bleeding. An overt bleed will be categorized as major if it fulfils at least one of the following criteria [24, 25]: (i) fatal; (ii) bleeding into a critical area or organ; (iii) surgical site bleeding that causes hemodynamic instability; (iv) non-surgical site bleeding causing a fall in hemoglobin level of ≥ 20 g L^−1^, or leading to transfusion of ≥ 2 units of whole blood or red blood cells; (v) surgical site bleeding that requires a second intervention (open, arthroscopic, endovascular), or hemarthrosis of sufficient size to delay mobilization or wound healing. Bleeding will be categorized as clinically relevant non-major if it does not meet the criteria for major bleeding, but results in hospitalization, aspiration of a wound, or a wound hematoma complicated by infection or any other non-major bleeding requiring medical attention. All other overt bleeding events will be considered minor.

Both the primary efficacy endpoint and the safety endpoint will be adjudicated by an independent critical events committee (CEC).

The EQ-5D-5L is a patient-reported outcome measure that provides a simple descriptive profile and a single index value for health status. The questionnaire entails 5 dimensions, including mobility, self-care, usual activities, pain/discomfort and anxiety/depression [26]. Patients will be asked to complete the questionnaire at baseline (Visit 1) and 90 days after surgery (Visit 5) (Table 2). The questionnaire will be administered at the beginning of the trial Visit, prior to any interaction with the trial investigator, including any tests, treatments or receipt of test/examination results. This is to avoid any possible influence on the subjects or their responses to the quality-of-life (QoL) questionnaire.

The Hip disability and Osteoarthritis Outcome Score (HOOS)-12, developed as a 12-item short form of the original 42-item HOOS [27], is one of the most widely used patient-reported outcome measures surrounding total hip arthroplasty [28, 29]. It assesses pain, function and quality of life. Patients will be asked to complete the questionnaire at baseline (Visit 1) and 90 days after surgery (Visit 5) (Table 2).

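### The stated model for quantitative outcomes leaves out the Visit 1 value of HOOS-12, EQ-5D-5L and mobility, which costs precision on these secondary outcomes but causes no bias

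*Protocol article*

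**What the plan says.** The Protocol article, Sample size calculation and statistical analysis, gives one rule for all quantitative outcomes: "Comparisons will be based on linear regression models with treatment as explanatory variable and adjusting for stratum", with stratified Wilcoxon-Mann-Whitney tests as the alternative. It names no other covariate.

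The strata are defined under Intervention and treatment regimens, trial flow. Randomization is done per site, and in addition "randomization will be stratified by concomitant single chronic antiplatelet medication (ASA or clopidogrel"). Neither factor carries a patient's own functional or quality-of-life score.

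The baseline values exist. For EQ-5D-5L, and in the same terms for HOOS-12, the Outcomes section says: "Patients will be asked to complete the questionnaire at baseline (Visit 1) and 90 days after surgery (Visit 5"). Table 2 marks TUG and active range of motion at Visits 1, 3 and 5.

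Table 3 lists three secondary endpoints that draw on these measurements:

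- "Changes in patient-reported hip joint-specific disability measured by the HOOS-12 score following surgery", which is a change score;
- "Generic quality of life measured by EQ-5D-5L", which is not worded as a change;
- "Patient mobility", which is also not worded as a change.

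**The concern.** In a linear model for a score measured before and after surgery, the baseline value is usually the strongest predictor available. The stated model handles it in one of two ways. For a change score, baseline is subtracted with its coefficient fixed at 1. For a day-90 score, baseline is ignored, so its coefficient is fixed at 0. Including it as a covariate lets the data estimate the coefficient, so in a trial of this size the treatment effect is estimated at least as precisely as under either fixed choice.

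At stake is the width of the confidence intervals for HOOS-12, EQ-5D-5L and mobility. Baseline adjustment would also make the result the same whether the outcome is entered as a change or as a day-90 value, a choice that Table 3 leaves open for EQ-5D-5L and mobility.

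**Working it through.** **The plan's own figure.** The article gives no sample size, standard deviation or correlation for these outcomes. Its only sample-size figure concerns the primary endpoint: 2,786 evaluable patients. That figure reproduces closely. With 1% in both arms, a margin of 0.01, one-sided 5% and 80% power, the restricted maximum-likelihood (Farrington-Manning) formula gives 2,768. An inflation of about 1.006 for the interim futility bound brings this to about 2,784. It is used here only for the arm size, 2,786 / 2 = 1,393.

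**Assumptions not in the article.** The correlation r between baseline and day 90 is taken as 0.3 to 0.5, within strata, because stratum is already in the model. The variance is taken as equal at both times.

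**Formulas.** The variance of the treatment effect, relative to a day-90-only analysis, is:

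- day-90 value only: 1
- change score: 2(1 − r)
- baseline-adjusted: 1 − r²

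The ratios for the adjusted model are therefore (1 − r²) / [2(1 − r)] = (1 + r)/2 against the change score, and 1 − r² against the day-90 value. The ratio of standard errors is the square root of each.

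| r | Variance ratio against change | SE reduction | Variance ratio against day 90 | SE reduction |
|---|---|---|---|---|
| 0.3 | 0.65 | 1 − √0.65 = 19% | 0.91 | 1 − √0.91 = 5% |
| 0.4 | 0.70 | 1 − √0.70 = 16% | 0.84 | 1 − √0.84 = 8% |
| 0.5 | 0.75 | 1 − √0.75 = 13% | 0.75 | 1 − √0.75 = 13% |

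**Detectable difference in SD units** (two-sided 5%, 80% power, 1,393 per arm): (1.960 + 0.842) × √(2k / 1,393), where k is the relative variance above.

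| r | Change score | Day 90 only | Baseline-adjusted |
|---|---|---|---|
| 0.3 | 0.126 | 0.106 | 0.101 |
| 0.4 | 0.116 | 0.106 | 0.097 |
| 0.5 | 0.106 | 0.106 | 0.092 |

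**Does the direction depend on the assumptions?** No. With standard deviations s0 at baseline and s1 at day 90, the change-score variance minus the adjusted variance is s0² + s1² − 2r·s0·s1 − s1²(1 − r²) = (s0 − r·s1)², which is never negative. Against the day-90 analysis the difference is r²·s1², also never negative. Only the size of the gain depends on r and on the two variances.

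**The case against.** The strongest reply is that the sentence is a generic rule for a type of outcome in a condensed article. It has to cover length of stay, which has no baseline, and covariates for single endpoints are normally set in the analysis plan, which is not shown and may add them. That is fair and limits how much weight the point can bear. It does not remove the point, because the article states which terms the comparison uses, and a plan that followed the text would omit baseline.

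Several further objections stand in full:

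- The method is not fixed as a linear model. The stratified Wilcoxon-Mann-Whitney alternative has no baseline term either, but the variance ratios above do not apply to it.
- A reader might infer that regression to the mean or baseline differences bias the comparison. The documents do not support this. Allocation is randomized 1:1, so regression to the mean affects both arms equally in expectation, and any baseline difference is due to chance. With 1,393 per arm, the standard error of a baseline mean difference is √(2 / 1,393) = 0.038 SD.
- A reader might apply the 13% to 19% figure to every outcome. It holds only against a change score, and only HOOS-12 is defined as one.
- Entry requires "Baseline TUG test scoring < 20 s, corresponding to a good mobility status before surgery". This restricts the baseline range and may lower r, and so the gain, for TUG.
- These are secondary outcomes, and the trial is sized for a 1% event rate. Detectable differences are already near 0.1 SD without adjustment.

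**Conclusion.** The point holds as one of efficiency. The stated analysis is valid under randomization but less precise than it could be with data that the trial already collects. For r of 0.3 to 0.5 and equal variances, both assumed, baseline adjustment would reduce the standard error by about 19% to 13% for HOOS-12 analysed as an unadjusted change. For EQ-5D-5L and mobility the reduction is about 5% to 13% if day-90 values are analysed. In detectable differences this is a gain of 0.126 − 0.101 = 0.025 to 0.106 − 0.092 = 0.014 SD against the change score, and of 0.106 − 0.101 = 0.005 to 0.014 SD against the day-90 value.

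A reader might infer that the trial's main conclusion is weakened. It is not: the primary VTE comparison and its sample size do not use this model.

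**What to change.** For each quantitative outcome measured at Visit 1 (HOOS-12, EQ-5D-5L, TUG, range of motion), state a linear regression with treatment, the full stratum adjustment already planned (site and antiplatelet use) and the outcome's own Visit 1 value. Site should stay in the model: randomization is done per site to account for local differences in the initial open-label anticoagulation. Outcomes without a baseline, such as length of stay, keep the stated model.

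The cost is one sentence in the analysis plan or in a protocol amendment. No visit, questionnaire or patient is added. The article reports 59 patients enrolled as of March 2025 and expects enrolment to finish in June 2027, so on that timetable the covariate can be fixed well before unblinding.

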### Interim analysis

After 3-month follow-up of the first 1,760 randomized patients, a formal interim analysis will be performed on the PP population by an independent statistician at a significance level α = 0.50, leading to stopping for futility if significance is not obtained. Based on the results of the interim analysis, the conditional power (CP) of the final analysis will be calculated. If CP > 90%, sample size will be reduced to provide 90% CP. The trial will also be stopped for futility if CP ≤ 50% or recalculation at interim analysis yields an overall sample size of > 3,200 patients (including follow-up losses) to obtain 80% CP. The first condition for stop for futility corresponds to a promising zone with a lower bound of CP_min_ = 50% which guarantees that the significance level is kept when the conventional test statistic is used [38]. The second condition is due to feasibility of recruitment. The sample size re-calculation will be performed according to [38].

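### The interim conditional power covers only the per-protocol test, but success needs both PP and mITT, so a cut to 90% conditional power need not leave 90% for the actual decision

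*Protocol article*

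**What the plan says.** All of this comes from the protocol article.

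- **Number of looks.** Under Sample size calculation and statistical analysis, the design is "a two-arm non-inferiority trial for a binary study endpoint with a single interim analysis".
- **Interim set.** Under Interim analysis, "a formal interim analysis will be performed on the PP population by an independent statistician", once the first 1,760 randomized patients have three months of follow-up.
- **What follows from it.** The test at level 0.50 works by "leading to stopping for futility if significance is not obtained". Then: "Based on the results of the interim analysis, the conditional power (CP) of the final analysis will be calculated". If CP exceeds 90%, the sample is reduced to give 90%. The trial stops if CP is 50% or less, or if 80% CP would need more than 3,200 patients.
- **Final decision.** Under Sample size calculation and statistical analysis, "the primary endpoint will be analyzed in both populations and non-inferiority will be declared if it can be established in both".
- **The two sets.** PP patients must have "completed the study without major protocol deviations". The mITT set "includes all randomized patients who underwent THA and received at least one dose of the study medication".

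The article gives the mITT set no part in the interim calculation.

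**The concern.** The quantity that the Interim analysis section presents as the CP of the final analysis is the CP of one of two tests that must both succeed. The PP set is defined partly by what happens after randomization. A patient who was operated on and dosed, had a VTE and had a major deviation counts in the final mITT test but not in the interim CP.

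The error runs one way. Joint CP cannot exceed PP CP, so the rule can only overstate the chance of success. This matters most for the reduction. A trial with PP CP above 90% gives up patients on the understanding that 90% remains, while the mITT test it must also pass may be well short of that.

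**Working it through.** **1. The plan's own sample size.** Inputs from the article: 1% vs 1%, margin 0.01, one-sided 5%, power 80%, 1:1 allocation, interim at 60%. With the Farrington-Manning normal approximation, the null standard deviation s0 is 0.15416 (restricted maximum likelihood) and s1 = √(2 × 0.01 × 0.99) = 0.14071:

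n per arm = [(1.6449 × 0.15416 + 0.8416 × 0.14071) / 0.01]² = 1,383.8

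The futility stop at level 0.50 at 60% information inflates this by 1.00635: 2 × 1,383.8 × 1.00635 = 2,785.2, or 2,786 after rounding up. This matches the article. Dividing by 0.95 gives 2,932.6 (stated 2,932). The figure is for a single test in a single set, with no allowance for a second test that must also pass.

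**2. Set sizes.** PP per arm is 1,760 × 0.95 / 2 = 836 at interim and 2,786 / 2 = 1,393 at the end. The PP share of mITT is not in the article. I took 95%, giving mITT of 836 / 0.95 = 880 and 1,393 / 0.95 = 1,466 per arm. That equals the randomized counts (1,760 and 2,932), so it assumes that everyone randomized is operated on and dosed. A 90% share with the same PP numbers would need 2 × 836 / 0.90 = 1,858 mITT patients at interim, more than the 1,760 randomized, so I do not use it.

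**3. Formulas.** z = (0.01 − difference) / SE with unpooled SE. CP under the observed trend (an assumption) at information fraction t is Φ[(z/√t − 1.645) / √(1 − t)], with t = 0.60. Joint CP is at most the smaller of the PP and mITT CPs.

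**4. One interim result.** PP events of 8 vs 8 in 836 per arm give z = 2.10 and CP = 0.95, so the reduction rule applies. Adding VTE in the 44 excluded patients per arm:

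| Events outside PP (experimental : control) | mITT events | mITT z | mITT CP at planned size |
|---|---|---|---|
| 1 : 1 | 9 vs 9 | 2.08 | 0.95 |
| 2 : 2 | 10 vs 10 | 1.98 | 0.92 |
| 3 : 1 | 11 vs 9 | 1.53 | 0.70 |

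Balanced events barely matter; a 3 : 1 split does. A reduction then makes it worse. If the final size were cut so that t = 0.8 (illustrative), mITT CP at z = 1.53 would be Φ[(1.53/√0.8 − 1.645)/√0.2] = Φ(0.15), about 0.56.

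**5. How often.** I ran 400,000 simulated trials per row, with true PP rates of 1% vs 1%. As a check, PP power at the planned size without interim stops is Φ(0.01/√(0.0198/1,393) − 1.645) = Φ(1.01) = 0.84. PP CP exceeds 90% in about 58% of trials.

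| Assumed rates outside PP (experimental vs control) | mITT CP ≤ 90%, among trials with PP CP > 90% | Joint power, planned size | PP power |
|---|---|---|---|
| 1% vs 1% | 5.5% | 83% | 84% |
| 2% vs 2% | 9.7% | 81% | 84% |
| 3% vs 1% | 19.3% | 76% | 84% |

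The second column understates the share with joint CP of 90% or less, because joint CP is no larger than either component.

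**The case against.** **The PP set was chosen for a reason.** The article argues that non-adherence dilutes differences in the ITT analysis and that blinding makes deviations similar in both arms, so PP is the harder test. That describes the average contrast. It does not make mITT pass whenever PP passes, and the article itself goes on to require both. What stands is that nothing in the documents points to imbalance outside PP. With balanced events the loss is only 1 to 3 points of power.

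**Stopping on PP is coherent.** A trial that fails PP fails the joint criterion, so a PP stop gives away nothing. Requiring both sets does not inflate type I error. Both points stand, and the PP futility stop need not change.

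**Two stronger readings are tempting.**
- A reader might infer that VTE in treated patients outside PP goes unwatched. The documents do not support this. These are futility and feasibility rules, and a condensed article may leave safety oversight to the full protocol.
- A reader might infer that a trial which PP continues and mITT would stop is bound to fail. In the same simulation, such trials are about 4%, 7% and 15% of those continuing in the three cases. At the planned size, about 82%, 79% and 72% of them still reach joint non-inferiority.

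**Conclusion.** The point holds, in limited form. The CP as defined is an upper bound on the CP of the decision that the trial will make, and the reduction rule does not secure the 90% it names. Under the 95% share and the unpooled test, the shortfall in joint power is about 1, 3 and 8 points in the three cases. The rule would allow a reduction despite mITT CP of 90% or less in about 5-6%, 10% and 19% of the trials eligible for one. The PP share, the event rates outside PP and the use of the observed trend are assumptions. The 3% vs 1% case shows sensitivity and is not a forecast. The mismatch itself needs no assumption: it lies between two explicit rules.

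**What to change.** In the Interim analysis section:

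1. Have the independent statistician compute the interim result and CP in both PP and mITT, or compute the joint CP directly.
2. Base the sample-size recalculation on the smaller CP, so that no reduction is made unless CP exceeds 90% in both sets.
3. State that CP refers to the joint PP-and-mITT decision.

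The PP futility stop and all thresholds can stay. Whether mITT should also trigger a futility stop is a trade-off for the sponsor. With equal 1% rates outside PP it adds about 3 points of stops and lowers overall success by about 2 points (64% to 62%). At 3% vs 1% it adds about 10 points of stops and lowers success by about 7 (61% to 54%).

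The cost is a second run of the same code and fewer or smaller reductions. With 59 patients enrolled as of March 2025 (Current enrollment status), against the 1,760 that trigger the look, the change could be made before any comparative data are seen.

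### The stated 80% global power matches a design with only the α = 0.50 futility stop; with the two conditional-power stops included it is about 55–72% at 1% vs 1%.

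*Protocol article*

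**What the plan says.** The section on sample size and statistical analysis describes a group sequential design with one look at 60% of patients, no efficacy stop, and a "global one-sided significance level of 5% and a global power of 80% was computed using a normal approximation". It then reports: "A sample size of 2,786 evaluable patients has been calculated", or 2,932 with 5% dropout. The margin is a risk difference of 0.01. For the control arm, "a 1.0% probability in the control arm remains an appropriate estimate", and for the experimental arm the text relies on "the assumption of a low frequency (1.0% or even less) of VTE events as per" the alternative hypothesis.

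The Interim analysis section sets three stops after 1,760 randomized patients, all worded as firm rules:
- a test at α = 0.50, "leading to stopping for futility if significance is not obtained";
- CP of 50% or less;
- "or recalculation at interim analysis yields an overall sample size of" more than 3,200, losses included, for 80% CP.

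If CP exceeds 90%, the sample size is reduced to give 90% CP. CP is to be based on the interim results, but the section does not say whether the assumed effect is the observed trend or the planned one. The lower CP bound is justified by control of the significance level with the conventional statistic, and the 3,200 limit by feasibility.

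**The concern.** A futility stop that acts often under the alternative costs power, and that cost belongs in the sample size. A stop at α = 0.50 costs almost nothing. A stop whenever 80% CP needs more than 3,200 patients allows only about 9% growth over 2,932 (3,200/2,932 = 1.091), so it should act often. If the 80% was computed without it, a short regimen exactly as good as the long one would face a substantial chance of being abandoned at 1,760 patients, and the power given to funders, ethics committees and readers would not be the power of the trial being run.

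**Working it through.** **Inputs (protocol article).** One-sided α 0.05, power 80%, margin δ = 0.01, 1% in both arms, 1:1 allocation, information fraction t = 0.6, 5% losses. Assumed: information is proportional to patients, and the 3,200 includes 5% losses (3,040 evaluable).

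**1. Reproducing 2,786.** Farrington–Manning normal approximation: N = 2[(z₀.₉₅·s₀ + z₀.₈₀·s₁)/δ]². The restricted estimates are 1.705% and 0.705%, so s₀ = 0.1542; s₁ = √(2 × 0.01 × 0.99) = 0.1407. Then N = 2[(1.645 × 0.1542 + 0.842 × 0.1407)/0.01]² ≈ 2,767.7. With a stop at z₁ ≤ 0 and final critical value 1.645, 80% power needs a drift of 2.494 instead of 2.486, an inflation of 1.00635. 2,767.7 × 1.00635 = 2,785.2, or 2,786 in two equal arms. Unpooled variance (2,450) and null variance (3,215) do not match.

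**2. Interim distribution at 1% vs 1%.** z₁ ~ N(2.494 × √0.6, 1) = N(1.932, 1).

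**3. CP at the observed trend.** At the planned size, CP = Φ[(z₁/√t − 1.645)/√(1 − t)].
- CP = 50% at z₁ = 1.645 × √0.6 = 1.274.
- CP = 80% at z₁ = √0.6 × (1.645 + 0.842 × √0.4) = 1.686.
- For the 3,200 rule, let R = 3,040/2,786 = 1.091. With the conventional statistic, 80% CP at R requires z₁ = (√t/R)[1.645√R + 0.842√(R − t)] = 1.638. With the conditional-error test it is 1.616. CP at the planned size is then 77% or 76%.

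| Stops applied | Stop if z₁ below | P(stop) | Power |
|---|---|---|---|
| α = 0.50 only | 0 | 2.7% | 80.0% |
| plus CP ≤ 50% | 1.274 | 25.5% | 68.9% |
| plus 3,200 rule | 1.616–1.638 | 37.6–38.4% | 58.9–59.6% |

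Power is P(z₁ above the bound and final z > 1.645), with correlation √0.6. Binomial simulation (400,000 runs, Farrington–Manning statistic) gives 36.9% stopping and 60.6% power. Adding the reduction to 90% CP gives about 55% power with the conditional-error test and about 61% with the conventional test.

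The 3,200 bound lies above the other two, so those never act alone. An increase is possible only for z₁ between 1.616–1.638 and 1.686, which has probability of about 2–3%.

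**4. CP at the planned effect.** CP = Φ[(√t·z₁ + (1 − t) × 2.494 − 1.645)/√(1 − t)]. The CP ≤ 50% stop is at z₁ = 0.835 and, without the 3,200 rule, leaves 76% power. The 3,200 rule is at about 1.398, with P(stop) = Φ(1.398 − 1.932) ≈ 30% and power about 66%. Across test statistics and reduction rules the range is 24–30% stopping and 63–72% power.

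**5. Sensitivity.** With a Wald statistic and observed-trend CP: 33% stopping, 65% power. With no dropout: 32–35% and 62–66%. With 0.7% in both arms and observed-trend CP: 20–25% stopping and 73–79% power, against 91–93% with the α = 0.50 stop alone.

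**6. Type I error (2% vs 1%).** About 2–4% with the stops as written.

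**The case against.** Four points deserve weight.

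- **A single figure is not supported.** A reader might infer that true power is 60%. That is one cell of a grid. The article does not define the effect behind CP, and it names both a conditional-error approach and the conventional statistic. Only the range can be stated. This objection stands.
- **Omission is inferred.** A reader might take it as established that the CP stops were left out, or that 2,786 is a miscalculation. No printed sum is wrong, and the article does not say how those stops were treated. The exact match with the α = 0.50 stop alone is strong evidence, not an admission.
- **The loss depends on the event rate.** The article allows for rates below 1% and cites 0.64–0.70% in the Canadian trial. At 0.7% in both arms power comes close to 80%. This stands, but the sample size and its 80% rest on 1%.
- **The stops are reasoned and do no harm to type I error.** Both have a stated purpose, and ending early at low CP is a legitimate resource choice. A reader might infer a raised risk of a false non-inferiority claim; the calculation shows the opposite. Still, protecting the significance level limits when the sample size may be increased, and feasibility limits how far. Neither makes 80% the power of a design that stops.

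**Conclusion.** The concern holds as an inconsistency between the stated power and the stated stopping rules. At 1% vs 1% every full-rule variant examined gives 55–72% power. With the Farrington–Manning statistic that reproduces 2,786, and CP at the observed trend, it is 55–61% with 37–38% stopping. With CP at the planned effect it is 63–72% with 24–30% stopping. Under the observed trend the promising zone, described as starting at 50% CP, in effect starts at 76–77% and is nearly empty.

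The result rests on the three stops being binding, as worded, and on information accruing with patients. Requiring success in both the per-protocol and modified intention-to-treat sets was not modelled and could only lower power. The harm is lost power, not false claims of non-inferiority.

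**What to change.** **Minimum change.** State which effect CP assumes and which final test is used, recompute global power with all interim rules, and report that figure (about 60% under the observed trend) with its range. This costs a calculation and a wording change. Restoring 80% by size alone, with the bound held at z₁ > 1.616, would need about 4,640 evaluable patients, far above 3,200.

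**Alternative.** Keep α = 0.50 as the only stop, use CP above 50% solely as the gate for an increase, and cap at 3,200 instead of stopping. The rule that reduces the sample size when CP exceeds 90% must be handled at the same time:
- Rule deleted: about 80.6% power and 4.9% one-sided type I error.
- Rule kept with a conditional-error test: about 77% power and 5.0%.
- Rule kept with the conventional statistic: about 6.2%, above the stated 5%. This combination must be avoided.

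**Cost of the alternative.** It is a substantive amendment to the adaptive rules of an enrolling trial, though only 59 patients had been enrolled by March 2025. At 1% vs 1% without the reduction, expected evaluable size rises from about 2,360 (0.384 × 1,672 + 0.616 × 2,786, where 1,672 = 0.95 × 1,760) to about 2,790. It never exceeds the 3,200 total already accepted.
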